#### Secondary outcome measures

The secondary outcome measures in this clinical trial will include the following assessments: Rhinoconjunctivitis Quality of Life Questionnaire score (RQLQs), acoustic rhinometry (AcRh), anterior rhinomanometry (AnRh), relief medication scores (RMs) and adverse events (AEs).

RQLQs is a questionnaire a questionnaire used to assess patients' quality of life, and consists of 28 questions grouped into seven domains, including activities, sleep, non-nose/eye symptoms, practical problems, nasal symptoms, eye symptoms, and emotional well-being. Each domain is ranked from no impairment to severe impairment on a scale of 0 to 6 [3, 8, 31]. The severity of symptoms during the trial will also be assessed using TNSS.

AcRh is a noninvasive and reliable method for studying the nasal cavity. It measures cross-sectional area and volume by analyzing acoustic reflections at various distances from the nasal inlet [32]. AcRh has been used to evaluate nasal dimensions in AR and assess the effectiveness of therapeutic interventions [33].

AnRh is a method designed to analyze the airflow through one nostril at a time based on trans nasal pressure. It is used to assess nasal air-space volume and patency and has become an international standard for estimating nasal resistance and flow [34].

RMs will be considered in evaluating the efficacy of the trial. The daily dose of anti-allergic medication, including antihistamines, decongestant nasal sprays, and eye drops, will be scored as 1 point. Orally administered antihistamines will be scored as 2 points, and steroid nasal sprays or eye drops will be scored as 3 points [35].

AEs will be monitored through self-reporting by the participants. Any undesirable experiences will be recorded on Case Report Forms (CRFs). Participants will have access to the research team for any concerns or issues. The occurrence time, severity, management, and causal relationship of AEs will be documented. All AEs will be followed up until resolution, and severe AEs will be promptly reported to the Ethics Committee of SCCGZUCM within 24 hours. A questionnaire will also be used to gather participants' opinions on the expectations of self-administered acupressure for AR and the credibility of the blinding method used in the study.

Additionally, the treatment mechanism of ARAT will be explored in this trial. Nasal secretions from eligible participants will be collected by research nurses at the beginning and end of the treatment. These biological specimens will be centrifuged and stored in the Biological Resource Center of SCCGZUCM for molecular analysis. Cytokines such as interleukin-5 (IL5), IL13, thymic stromal lymphopoietin (TSLP), and interferon-gamma (IFN-γ) will be detected using the enzyme-linked immunosorbent assay (ELISA) method.

Among these outcome measures, TNSS and RQLQs will be assessed at the beginning, middle, and end of treatment period, as well as during the follow-up period at weeks 4, 8, and 12. The other measures will be assessed at the beginning and end of the treatment period.

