#### Drugs

Participants in all three groups will be administered the same medication, which is mometasone furoate nasal spray (50μg once daily, Zhejiang Xianju Pharmaceutical Co., Ltd., Batch number: H20113481), as the routine treatment during the intervention period. Additionally, for symptom control throughout the study, participants will use cetirizine hydrochloride tablets (10mg, Chengdu LEER Pharmaceutical Co., Ltd., Batch number: H20020250).

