### Ethical approval

The study protocol complied with the ethical standards described in the Declaration of Helsinki. All methods of this study will be performed in accordance with the relevant guidelines and regulations. The Ethics Committee of Guangdong Provincial Hospital of Chinese Medicine has approved the study protocol for this trial (Approval number: ZF2023-040-01), and it has been registered on the Chinese Clinical Trial Registry (Trial registration number: ChiCTR2300072292. Registered on June 08, 2023). Each participant will have sufficient time to decide whether to participate in the trial or not and written informed consent must be obtained before randomization. Cetirizine Hydrochloride tablets will be provided if AR attacks interfere with participants' quality of life. Participants will be required to document relief medication use in their diaries. Any alterations or modifications to the study protocol must be communicated to the Ethics Committee of Guangdong Provincial Hospital of Chinese Medicine, Guangzhou, China, and reported to the Chinese Clinical Trials Registry. Written informed consent will be obtained from the patients and be aware of the potential benefits and risks.

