## Discussion

In China, a multicenter study found that the majority of AR patients have persistent symptoms with or without seasonal aggravation [37]. Previous trials evaluating the effect of acupressure on AR did not differentiate between SAR and PAR. Considering of the characteristics of AR, only PAR patients clinically diagnosed with symptoms lasting for at least 6 months per year will be enrolled in this trial.

Intranasal corticosteroids are considered the first-line pharmacological treatment for AR due to their safety, fast action, and ability to alleviate symptoms, decrease mucus membrane permeability, and improve quality of life [1, 38]. Two long-term studies [39, 40] evaluating the safety of mometasone furoate nasal spray in children or adolescents with AR yielded positive results. Therefore, mometasone furoate nasal spray will be used as the routine treatment in this trial.

Acupuncture, a long-standing non-pharmacological treatment for AR, has been recommended as an effective alternative for symptom alleviation, improved quality of life, and reduced medication side effects [41], with supporting evidence from numerous randomized clinical trials.

Mechanisms of acupuncture for AR have also been extensively studied. Lei RL and colleagues [19] demonstrated that acupuncture exhibits anti-inflammatory and antihistaminic effects by effects by downregulating proinflammatory cytokines and neuropeptides. A recent review [42] summarized that acupuncture modulates anti-inflammatory actions in AR through various pathways, including upregulating Th1 cytokines, downregulating Th2 and proinflammatory cytokines, and affecting proinflammatory neuropeptides and neurotrophies. Clinical studies on AR patients have suggested that acupuncture treatment improves the balance between T-helper 1 (Th1) and T-helper 2 (Th2) cell-derived pro-inflammatory versus anti-inflammatory cytokines, as evidenced by differential gene expression in peripheral blood before and after acupuncture therapy [26].

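### The relief medication score does not exclude the routine mometasone spray, lets oral cetirizine fit two point classes, and is not scheduled after the end of treatment

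*Protocol article*

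**What the plan says.** **Scoring rule (Protocol article, Secondary outcome measures).** The lowest class is "The daily dose of anti-allergic medication, including antihistamines, decongestant nasal sprays, and eye drops, will be scored as 1 point". The next sentence sets the two higher classes: "Orally administered antihistamines will be scored as 2 points, and steroid nasal sprays or eye drops will be scored as 3 points". The same section says that the score will count towards the evaluation of efficacy. The abstract names the outcome as a change in score.

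**Trial drugs (Drugs; Discussion; Ethical approval).** "Participants in all three groups will be administered the same medication, which is mometasone furoate nasal spray", given "as the routine treatment during the intervention period". The Discussion introduces intranasal corticosteroids as first-line treatment and concludes: "Therefore, mometasone furoate nasal spray will be used as the routine treatment in this trial". Cetirizine tablets are the symptom-control drug for the whole study and are supplied when attacks interfere with quality of life.

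**Timing.** After giving TNSS and RQLQs a schedule that runs to follow-up week 12, the outcome section says: "The other measures will be assessed at the beginning and end of the treatment period". The relief score is among those other measures. The opening of the Outcomes section says that outcomes will be compared between groups at baseline, at the end of treatment and at the end of follow-up. Under Ethical approval: "Participants will be required to document relief medication use in their diaries".

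**The concern.** A relief medication score should show how much extra medication a participant needed on top of the treatment everyone gets. Here the rule works by drug class alone, and the drug everyone gets belongs to the most heavily weighted class. If whoever computes the score follows the wording, most of it can be background treatment, and a participant who takes the routine spray more faithfully looks worse.

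Two further features leave the result open. The relief drug that the trial supplies is an oral antihistamine, and both the 1-point and the 2-point sentence can be read to cover it. The score also has no scheduled assessment after treatment ends, although symptoms are followed for 12 more weeks with cetirizine still available. Follow-up TNSS would then have no scheduled relief score beside it.

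Two analysts could therefore derive different scores from the same diary. The trial is open-label, so these choices should be fixed before data are seen.

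**Working it through.** The article states no total for this score, so there is no figure to reproduce. The check is arithmetic on the stated points, followed by a comparison of the sections.

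**Inputs from the article.** Steroid nasal spray 3 points; oral antihistamine 2 points; antihistamine with no route stated 1 point; mometasone spray once daily in all arms during the intervention; intervention 4 weeks = 28 days; follow-up 12 weeks.

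**Assumed inputs.** Number of cetirizine days and spray adherence. Neither is given, so ranges are shown.

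**1. Size of the addition if the spray is counted.** 3 × 28 = 84 points for a fully adherent participant in any arm.

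**2. Share of the total due to the spray.** With k cetirizine days at 2 points, the share is 84 / (84 + 2k).

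| Cetirizine days k | Total without spray | Total with spray | Spray share |
|---|---|---|---|
| 5 | 10 | 94 | 89% |
| 10 | 20 | 104 | 81% |
| 20 | 40 | 124 | 68% |
| 28 | 56 | 140 | 60% |

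**3. Between-arm comparison.** Let p be the proportion of spray days taken. The spray contributes 84 × p, so the artefact in a difference between arms A and B is 84 × (pA − pB). At equal adherence it is zero. Otherwise the arm with better adherence scores higher, that is, worse:

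| Adherence gap | Points over 28 days | Cetirizine days at 2 points |
|---|---|---|
| 10% | 8.4 | 4.2 |
| 20% | 16.8 | 8.4 |
| 30% | 25.2 | 12.6 |

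**4. Change from baseline.** The spray is described for the intervention period only. A participant with no steroid spray in the baseline score therefore rises by up to 3 points a day in any arm, whatever the need for relief. The shift is smaller for anyone whose baseline score already includes such a spray.

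**5. Class of cetirizine.** A 10 mg tablet is an antihistamine (1 point) and an orally administered antihistamine (2 points). Ten tablet days score 10 or 20, a factor of two.

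**6. Timing.** The Outcomes section promises a comparison at the end of follow-up. The later schedule sentence confines the relief score to the start and end of treatment. The Drugs section keeps cetirizine in use for the whole study, and the diary records relief use. So the data are to be collected, but no score is scheduled from them in the 12 follow-up weeks. Table 1 is not reproduced in the text available, so this rests on the prose.

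**The case against.** The strongest reply is that the protocol keeps the two roles apart. Mometasone is called routine treatment, cetirizine is the symptom-control drug, and both the outcome and the diary are named for relief medication. A reader might infer from the 3-point class that the protocol declares the routine spray to be relief medication. It does not say so, and its labels point the other way. What stands is that the rule assigns points by class of anti-allergic medication, not by role, and contains no exclusion.

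Second, all arms get the same spray, so the addition is common to them. That is correct at equal adherence. A reader might infer a bias against the acupressure arms because they have weekly video calls. The documents do not support this. The calls are for monitoring acupressure technique, no adherence figures are given, and the non-specific acupoint group follows the same procedure as the ARAT group, so this route would leave the comparison of those two arms untouched. Unequal adherence is a possibility that the rule leaves unguarded, not an established difference.

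Third, a specific sentence after a general one can be read as a carve-out, leaving the 1-point class for non-oral antihistamines. If only cetirizine is used and one value is applied throughout, choosing 1 or 2 merely rescales the score and alters no standardised difference or rank test. Both points are fair. The choice matters when products are mixed or coders differ. A similar overlap might be inferred for eye drops, but it disappears if the word steroid governs both nouns in the 3-point class, which is a natural reading.

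Fourth, a reader might infer that relief use between the two assessments is lost. The diary and the abstract's statement that rescue need will be recorded contradict that: an end-of-treatment score could draw on the interval. The way diary days are aggregated is also commonly left to an analysis plan. The point that stands is the mismatch between the promised follow-up comparison and a schedule without a follow-up score.

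**Conclusion.** The concern holds in a limited form, as a defect in how one secondary outcome of an exploratory trial is defined.

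- **Missing exclusion.** Taken literally, the rule adds up to 84 points over 28 days in every arm. This is 60% to 89% of the total for 28 down to 5 assumed cetirizine days at 2 points, with full spray adherence. It shifts change from baseline, and it costs an arm 8.4 points for each 10 percentage points of better adherence.
- **Ambiguous class.** The supplied relief drug can score 1 or 2.
- **Schedule.** No relief score is planned after treatment, against the statement that outcomes are compared at the end of follow-up.

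The article does not establish that the spray was meant to count, that adherence will differ between arms, or that interval use goes unrecorded. The sizes above apply only if the rule is followed as worded. The primary outcome definition is unaffected; what suffers is the reading of TNSS beside relief use.

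**What to change.** Reconcile the Drugs, Outcomes, Secondary outcome measures and Ethical approval sections on three points:

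1. State that the protocol-supplied mometasone spray is excluded from the relief medication score, and report adherence to it separately by arm.
2. Make the classes mutually exclusive: the 1-point antihistamine entry covers non-oral products only, and the 1-point eye-drop entry covers non-steroid drops only. Oral antihistamines then score 2, and steroid products other than the routine spray score 3.
3. Define the outcome as the mean daily diary score over the 4 treatment weeks and, from the same diary, over the follow-up period. The schedule then matches the promised comparison at the end of follow-up.

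The cost is a few sentences of outcome definition and slightly more diary data entry. The score might depart a little from the cited scale, which cannot be checked here. The change concerns scoring only and proposes nothing about any drug, dose or rescue rule. It should be made before any outcome data are examined by arm.

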**Methods/design:**

In this trial, eligible 111 participants diagnosed with PAR will be randomly assigned to one of three groups: the ARAT group, the non-specific acupoints group, or the blank control group. The primary outcome will be the change in the total nasal symptom score, and the secondary outcomes will include: 1) changes in the scores of the standard version of Rhinoconjunctivitis Quality of Life Questionnaire (RQLQs); 2) acoustic rhinometry and anterior rhinomanometry; 3) changes in the scores of relief medication usage; 4) incidence of adverse events. Additionally, we will measure and compare the changes in cytokine levels (IL-5, IL-13, IFN-γ, and TSLP) in nasal secretions.

The RQLQs and primary outcomes will be assessed at the beginning, middle, and end stages of the treatment period, with monthly follow-ups conducted over a total of three months. The secondary outcomes and biomarkers in nasal secretions will be measured at the beginning and end of the treatment period. Any adverse events or need for rescue medication will be carefully noted and recorded.

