### Outcomes

This clinical trial will assess primary and secondary outcome measures. The outcomes will be compared between the groups at baseline, at the end of the treatment period, and at the end of the follow-up period. The recruitment, intervention, and assessment schedule for the randomized controlled trial is presented in Table 1.

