### Safety assessment

Participants will be asked to report any AEs, which are defined as any undesirable experiences [36]. They will have access to the research team members at any time. The occurrence time, severity, management, and causality of AEs will be recorded on CRFs. All AEs will be followed up until resolved, and severe AEs will be reported to the Ethics Committee of SCCGZUCM within 24 hours. Monitoring AEs in this trial serves the purpose of ensuring participant safety and dealing with adverse events in a timely manner, in addition to being a secondary outcome measure.

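### The adverse-event outcome window is contradictory: the outcome schedule closes it with the 4-week treatment, while the safety text leaves it open and fixes no enquiry in the 12-week follow-up

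*Protocol article*

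**What the plan says.** Under Secondary outcome measures, the protocol article names the secondary outcomes. The list ends with "relief medication scores (RMs) and adverse events (AEs", so AEs are formally an outcome and not only a safety-monitoring item.

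The same section closes with the timing. TNSS and RQLQs are taken at the start, middle and end of treatment, "as well as during the follow-up period at weeks 4, 8, and 12". For everything else, "The other measures will be assessed at the beginning and end of the treatment period". The abstract (Methods/design) agrees: "The secondary outcomes and biomarkers in nasal secretions will be measured at the beginning and end of the treatment period".

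Other sections treat AEs differently:

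- **Safety assessment**, and the AE paragraph under Secondary outcome measures: participants report any undesirable experience, its time of occurrence goes on the CRF, and each event is followed to resolution. On contact with the team, "They will have access to the research team members at any time". No end date is given.
- **Abstract**: a separate sentence, without a time limit, says that AEs will be recorded.
- **Outcomes**: the groups are compared "at baseline, at the end of the treatment period, and at the end of the follow-up period".
- **Drugs**: mometasone is confined to the intervention period, but "for symptom control throughout the study, participants will use cetirizine hydrochloride tablets".
- **Design**: a 2-week run-in, 4 weeks of intervention and 12 weeks of follow-up.

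**The concern.** The AE outcome has two possible windows, and the text does not choose between them. By the schedule sentences, AE incidence is a 4-week outcome. By the safety text and the end-of-follow-up comparison, it is a 16-week outcome. Two analysts working from the same article could report different incidences, and each could cite the article in support.

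The second problem is practical. Every participant is to be assessed three times in follow-up for TNSS and RQLQs, but the text attaches no AE enquiry to those contacts. Allocation is open to participants and investigators. If follow-up events enter the data only when a participant chooses to come forward, completeness may vary between people and could vary between arms. A question put to everyone in the same form at the same times would reduce that risk.

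Safety is in the trial's title, and the abstract's discussion expects the data to support it. The period over which safety is described should be fixed before the data are seen.

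**Working it through.** The plan states no figure that could be reproduced here, so the check is a comparison of the text plus one piece of arithmetic.

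**Step 1. Are AEs within the catch-all sentence?** The Secondary outcome measures section lists RQLQs, acoustic rhinometry, anterior rhinomanometry, relief medication scores and AEs, and then adds the cytokines. The timing paragraph takes TNSS and RQLQs out and assigns the rest to the beginning and end of treatment. AEs are in the list and are not taken out. Read literally, they are included.

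**Step 2. Is it a single slip?** No. The abstract names AE incidence as its fourth secondary outcome and then gives the same two time points for the secondary outcomes. RQLQs, also a secondary outcome, has its own schedule in the preceding sentence, so the abstract does make exceptions. It makes none to the timing of AEs, although its next sentence says that they will be recorded.

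**Step 3. What window does each place imply?**

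| Place | Implied AE window |
|---|---|
| Secondary outcome measures, timing paragraph | weeks 0–4 |
| Abstract, timing sentence | weeks 0–4 |
| Abstract, AE recording sentence | no limit stated |
| Secondary outcome measures, AE paragraph | no limit stated |
| Safety assessment | no limit stated |
| Outcomes, comparison times | to the end of follow-up, if AEs are included |

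**Step 4. How much time is in dispute?** From the Design section, time after the start of treatment is 4 + 12 = 16 weeks. Follow-up is 12 of those 16 weeks. Cetirizine use extends through them.

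**Step 5. Do contacts already exist in that time?** Yes. Follow-up weeks 4, 8 and 12 fall at 4 + 4 = 8, 4 + 8 = 12 and 4 + 12 = 16 weeks from the start of treatment. The last coincides with the final comparison time in the Outcomes section.

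**The case against.** The best defence is that AE collection has its own section, and a specific section should govern over a general closing sentence. Participants are to be asked to report any AE, can reach the team whenever they wish, and have the time of occurrence recorded, which makes most sense for continuous collection. The closing sentence follows the cytokine text and suits rhinometry, rhinomanometry and cytokines, which are point measurements. AE incidence is not something one measures at the beginning of treatment. The defence can add that Table 1 holds the visit schedule and that an article often leaves AE query wording to the full protocol and CRF.

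Much of this stands, and it rules out several stronger readings that a reader might infer:

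- **That no AE assessment is planned in follow-up, or that AEs are assessed only twice.** The safety text plans open-ended reporting with no cut-off at week 4.
- **That reports would be wholly unprompted.** The Safety assessment section says participants will be asked to report. What the text lacks is a stated time in follow-up when they are asked.
- **That a safety comparison at the end of follow-up is explicitly promised.** The Outcomes section speaks of outcomes in general. Rhinometry and rhinomanometry have no follow-up measurement in the timing paragraph, so the comparison sentence cannot apply to every outcome at every time. That it covers AEs is an inference.
- **That the trial is powered for safety.** The Sample size section rests on TNSS alone.
- **That the 12 of 16 weeks gives the share of events that would be missed.** It is a share of calendar time. The document gives no AE rates.

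The defence does not remove the contradiction. The Safety assessment section itself distinguishes monitoring for participant safety from AEs as a secondary outcome, and the only time points stated for that outcome are the two in the timing paragraph, repeated in the abstract.

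**Conclusion.** The point holds as an inconsistency to be reconciled, of minor to moderate weight. The text supports both a 4-week and a 16-week AE outcome window, and it names no AE enquiry at the three follow-up contacts. The disputed stretch is 12 of 16 weeks. The number of events affected cannot be estimated from the document.

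The conclusion assumes a literal reading of two sentences that agree with each other. It also depends in part on Table 1, whose content could not be read for this review. If Table 1 shows AE collection through follow-up, the intended window is clear and only the wording has to change. If it shows AEs at the beginning and end of treatment only, the safety text and the table conflict, and the matter is more than wording.

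**What to change.** 1. Exempt AEs from the closing timing sentence under Secondary outcome measures and from the matching abstract sentence, and bring Table 1 into line if it differs.
2. State in the Safety assessment section that AEs are collected in all three arms from the start of treatment to follow-up week 12.
3. Add one standard AE question, worded identically for every arm, to the existing TNSS and RQLQs contacts at follow-up weeks 4, 8 and 12. Self-report between contacts continues as described.
4. Report AE incidence separately for the 4-week treatment period and the 12-week follow-up period, so that neither is read as the other.

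The cost is a wording change, one CRF item and slightly more data entry. No visit is added and no treatment changes. Recruitment is stated to have begun on July 1, 2023, so the change should be notified to the ethics committee and the registry as the Ethical approval section requires. Participants who have already passed a follow-up contact should be identified in the report as not having been asked the standard question there.
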